#### Exploratory Hypotheses (Aim 4)

The Helipad program will be cost-effective relative to the active control (psychoeducation) at the 6-month follow-up from health sector and societal perspectives relative to the willingness-to-pay thresholds identified by the Productivity Commission report on mental health [29].

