#### Secondary Outcomes

Effectiveness will be compared between the Helipad co-designed interactive program condition and the standard psychoeducation web-based program condition for mental illness stigma, mental health literacy, and help-seeking attitudes (hypothesis 2), which will be assessed, respectively, based on reduced mental health stigma (Stigma and Self-Stigma Scales [40]), increased mental health literacy (Anxiety Literacy Questionnaire [A-Lit] and Depression Literacy Questionnaire [D-Lit] composite measure [41,42]), and increased help-seeking attitudes (Attitudes Toward Seeking Professional Psychological Help Scale-short form [43]) over time relative to the control condition.

In addition, we will examine the comparative effectiveness of the Helipad co-designed interactive program condition and the standard psychoeducation web-based program condition on reducing symptoms of mental ill-health and increasing quality of life and functioning (hypothesis 4). This will be determined based on reduced symptoms over time of depression (Patient-Reported Outcomes Measurement Information System [PROMIS] Depression short form scale [44]), anxiety (PROMIS Anxiety short form scale [44]), and general psychological distress (Distress Questionnaire-5 [DQ5] [45]) and increased scores on the Recovering Quality of Life (ReQoL-10) Questionnaire [46] and increased work and activity functioning (Work Productivity and Activity Impairment [WPAI] questionnaire [47]).

Finally, the relative effects of the program on increasing help-seeking behavior (hypothesis 3) will be assessed by the proportion of participants who reported seeking help from a professional source (defined as a psychologist or counselor, a psychiatrist, a family doctor or general practitioner [GP], or an EAP) in the past 6 months. We anticipate that this will be greater in the Helipad co-designed interactive program group among people with elevated symptoms of depression or anxiety relative to the control condition (standard psychoeducation only).

The primary end point for changes in mental health literacy is the posttest assessment, while for the other secondary outcomes, the 6-month follow-up assessment will be the primary end point as these outcomes take longer to elicit change.

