### Data Analysis

An intention-to-treat approach to account for missing data of the mixed model repeated measures ANOVA (continuous data) or mixed effects logistic regression (binary data) will be used, adjusting for intraclass correlation to account for clustering effects within each site. Mixed models include all available data and account for within-individual variability, including those participants with missing data points, under the missing-at-random assumption [48].

Exploratory analyses will examine evidence for moderators or mediators of outcome and will be reported separately from the primary and secondary outcomes. Implementation outcomes at 6 months will be separately examined using description statistics, including *t* tests (2-tailed). The economic analysis will examine cost-effectiveness from the health sector and societal perspectives. The cost of the Helipad intervention and the active control program will be estimated using microcosting methods. Service use data will be limited in this study to health care professional visits or services accessed (internet program and helpline) specifically for mental health. The additional costs of health care resource use will be operationalized as the number of contacts with health professionals collected on the Actual Help-Seeking Questionnaire [49] (psychologist or counselor, psychiatrist, family doctor or GP, EAP, phone helpline, and internet-based treatment program). Lost productivity will also be evaluated in societal perspective costs as assessed through the WPAI questionnaire [47] and valued using the human capital approach. The ReQoL-10 Questionnaire [46] will be used to calculate utility values and quality-adjusted life years (QALYs) using the area under the curve method. Differences in costs between trial groups will be compared to the differences in QALYs through an incremental cost-effectiveness ratio (ICER) because of the inherent value-for-money connotations associated with cost-effectiveness ratios using QALYs. Additional ICERs using secondary outcomes will be calculated where the Helipad intervention is found to have an effect. Nonparametric bootstrapping will be used to determine CIs for ICERs.

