### Power and Recruitment

Our study’s power and sample size estimations were informed by the primary outcome measure: the level of intention to seek help from professional sources, as measured by the GHSQ. Using data from the MATES in Construction workplace trial [61], a conservative intraclass correlation of 0.02 was assumed to estimate the design effect. An RCT [62] exploring the potential effectiveness of a web-based program designed to increase help-seeking intentions for social anxiety disorder informed the anticipated difference between pre- and posttest GHSQ scores (standardized mean difference=0.2). Because the size of the workplace clusters could not be anticipated ahead of time, a conservative average cluster size ranging from 25 to 35 was assumed. We assumed 15% attrition in participant numbers from pre- to postintervention, a conservative assumption based on previous workplace trials [63] and accounting for the single-session nature of the intervention. To detect an effect size of Cohen *d*=0.2 between the intervention and comparison arms with 80% power, using a 2-tailed type I error level of 0.05, we need to recruit between 30 and 36 workplaces (assuming each workplace has 25 to 35 participants), resulting in a minimum of 900 employees.

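### The additional, non-QALY ICERs are calculated only for secondary outcomes on which an effect is found, so these supplementary ratios are selected on the result and tend to understate cost per unit of effect

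*Protocol article*

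**What the plan says.** All places are in the protocol article.

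- **Main ratio (Data Analysis).** "Differences in costs between trial groups will be compared to the differences in QALYs through an incremental cost-effectiveness ratio (ICER"). The ReQoL-10 "will be used to calculate utility values and quality-adjusted life years (QALYs) using the area under the curve method". Neither step depends on what the trial finds.
- **Supplementary ratios (Data Analysis).** "Additional ICERs using secondary outcomes will be calculated where the Helipad intervention is found to have an effect". The sentence names no outcomes and does not say what counts as an effect, at which time point, or in which direction.
- **Uncertainty (Data Analysis).** "Nonparametric bootstrapping will be used to determine CIs for ICERs".
- **Perspectives (Data Analysis).** "The economic analysis will examine cost-effectiveness from the health sector and societal perspectives".
- **Pool of outcomes (Secondary Outcomes).** Stigma, mental health literacy, help-seeking attitudes, help-seeking behaviour, and the measures for "reducing symptoms of mental ill-health and increasing quality of life and functioning (hypothesis 4"). Under Work and Activity Functioning, the WPAI alone gives four percentage scores.
- **Criterion for value for money (Exploratory Hypotheses, Aim 4).** Cost-effectiveness is judged "relative to the willingness-to-pay thresholds identified by the Productivity Commission report on mental health". The economic aim is exploratory, both there and under Aims.

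**The concern.** The condition lets the result decide which supplementary ratios exist. That has two consequences.

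First, an outcome with no demonstrated effect gets no ratio. A program that costs more for no demonstrated gain is itself an economic finding, and the supplementary set cannot show it.

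Second, if the condition is a significance test, every effect used as a denominator has already passed that test and is biased away from zero on average. Dividing a given cost by an inflated effect makes each unit of benefit look cheaper than it is. Resampling the selected outcome's data treats it as if it had been fixed beforehand, so the bootstrap interval ignores the selection step.

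The article's Conclusions tie a positive result to rapid scale-up and to work with employers and insurers. Such readers may find a cost per additional person seeking help easier to use than a cost per QALY. Under this rule they would see it only if help-seeking behaviour passed the test.

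Cost-effectiveness analysis concerns the joint uncertainty of cost and effect. The article follows that principle for QALYs and departs from it for every other outcome.

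**Working it through.** The article gives no figure for this rule, so there is nothing to reproduce. Its sample-size inputs are used only to set a plausible standard error.

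**Inputs from Power and Recruitment:** 900 recruited, 15% attrition from pre to post, intraclass correlation 0.02, clusters of 25 to 35, two-sided alpha 0.05, and "standardized mean difference=0.2" for the primary outcome.

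**Assumptions added here:** an effect means a favourable result with z > 1.96; estimates are normal and in SD units; no baseline adjustment; incremental cost fixed; true secondary effects of 0.05 to 0.20.

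**Step 1. Standard error.** Analysed: 900 × 0.85 = 765.

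- 36 workplaces of 25: 21.25 analysed each; design effect 1 + 20.25 × 0.02 = 1.405; effective n = 765/1.405 = 544; SE = 2/√544 = 0.086.
- 30 workplaces of 30: 25.5 analysed each; design effect 1 + 24.5 × 0.02 = 1.49; effective n = 765/1.49 = 513; SE = 2/√513 = 0.088.

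**Step 2. Mean estimate among retained results.** For an estimate X ~ N(d, SE²), with φ and Φ the standard normal density and distribution function,

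E[X | X > 1.96 SE] = d + SE × φ(a)/(1 − Φ(a)), where a = 1.96 − d/SE.

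Example, d = 0.10 and SE = 0.0857: a = 0.793; φ(a) = 0.291; 1 − Φ(a) = 0.214; mean = 0.10 + 0.0857 × 1.362 = 0.217, which is 2.2 times the truth.

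| True d | Mean retained, SE 0.086 | Factor | Mean retained, SE 0.088 | Factor |
|---|---|---|---|---|
| 0.05 | 0.207 | 4.1 | 0.213 | 4.3 |
| 0.10 | 0.217 | 2.2 | 0.223 | 2.2 |
| 0.15 | 0.230 | 1.5 | 0.236 | 1.6 |
| 0.20 | 0.249 | 1.25 | 0.254 | 1.3 |

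**Step 3. Cost per unit of effect.** At fixed incremental cost, true effect divided by mean retained effect (SE 0.086) is 0.24, 0.46, 0.65 and 0.80 for true d of 0.05, 0.10, 0.15 and 0.20. The supplementary ratio would look roughly that fraction of its true value.

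**Step 4. Sensitivity to baseline adjustment.** With an assumed pre-post correlation of 0.55, the SE falls to 0.088 × √(1 − 0.55²) = 0.074. The factors at 0.10, 0.15 and 0.20 become about 1.9, 1.4 and 1.1. The bias shrinks but does not vanish. Attrition above 15% at 6 months, where the article states no figure, would push the other way.

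**Step 5. The main ratio.** The cost-per-QALY calculation has no selection step, so these factors do not apply to it.

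**The case against.** The strongest objection concerns scope. A reader might infer that the cost-effectiveness results as a whole are selected and overstate value for money. The documents do not support that:

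- The cost-per-QALY ratio is calculated whatever the result, and the article chooses it for its value-for-money meaning.
- The willingness-to-pay thresholds are nowhere tied to the supplementary ratios.
- The economic aim is exploratory.

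A reader might also infer that null outcomes will be hidden or that only favourable effects qualify. Neither follows. The Results section plans publication of the secondary outcomes and the economic analyses, and proportions improving, declining and unchanged will be reported. What is left out is the cost-effect pairing for outcomes without a demonstrated effect. The sentence refers to an effect, not a favourable one, so an adverse effect could also trigger a ratio. ReQoL-10 enters the economic analysis through the QALYs regardless, and WPAI productivity loss already enters the societal costs.

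The size of the bias is also open to challenge. It is an average, not a statement about each ratio: at a true difference of 0.20 a significant estimate can fall below the truth, since the threshold is 1.96 × 0.086 = 0.168. Holding cost fixed is a simplification. For help-seeking behaviour, the Actual Help-Seeking Questionnaire supplies both the effect and the contacts that are costed, so a chance-high effect may raise cost too and the ratio need not fall in proportion. The 2.2-fold figure needs an assumed effect of 0.10; the only effect size in the article, 0.2 for the primary outcome, gives 1.25 to 1.3.

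Finally, the condition has a rationale: a ratio with a near-zero denominator is unstable. That is a reason not to print the ratio. It does not justify omitting the incremental cost, incremental effect and their joint uncertainty.

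These points limit the scope and size of the concern. They do not remove the selection, which the sentence itself creates. Defining the threshold in an analysis plan would leave the conditioning in place, and the exploratory label does not undo it.

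**Conclusion.** The point holds for the supplementary, non-QALY ratios only. As written, that set depends on the result. If finding an effect means statistical significance, the denominators are exaggerated on average by about 1.25 to 1.3 times at a true difference of 0.20 and about 2.2 times at an assumed 0.10. Cost per unit of effect would then tend to be understated, and the planned bootstrap intervals would not correct for it.

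The figures rest on the significance reading, assumed true effects, pre-to-post attrition applied to outcomes whose end point is mostly 6 months, fixed incremental cost and no baseline adjustment. Overstatement is an expected tendency of these ratios, not an established result for any one of them. The main cost-per-QALY ratio and the value-for-money hypothesis are untouched. This is an inexpensive improvement to an exploratory analysis.

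**What to change.** In Data Analysis, delete the condition and name in advance a short list of secondary effect measures for the additional cost-effectiveness analyses. Professional help-seeking at 6 months, the Hypothesis 3 outcome, is one candidate; the choice belongs to the investigators.

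For each listed measure, report incremental cost, incremental effect and the bootstrap cost-effectiveness plane whatever the result, and give the ratio only where it can be interpreted. Label any further ICER chosen after seeing the results as selected and exploratory.

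For the listed measures this removes the selection, so the exaggeration factor returns to 1.0. The cost-per-QALY analysis does not change.

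The costs, outcomes and bootstrap are already planned, so the price is a sentence or two of text and a few more outputs. The one drawback is that some ratios will be unstable where the effect is near zero; there the plane carries the information.

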## Methods

### Trial Design

A 2-arm cluster RCT will test whether the Helipad co-designed interactive program increases help-seeking intentions in employees in workplaces more than the standard psychoeducation-alone program. Workplaces will be randomly allocated using minimization processes to either (1) the active intervention condition comprising the Helipad program or (2) an active control condition (a web-based time-matched standard psychoeducation program). Help-seeking intentions will be assessed at the individual level accounting for clustering by workplace. Self-report assessments will be conducted on the web at preintervention, immediately postintervention, and at the 6-month follow-up. This study protocol addresses the Standard Protocol Items: Recommendations for Interventional Trials (SPIRIT) checklist [30].

The flow of participants through the study is presented in Figure 1.

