### Data Collection

#### Overview

Participants who agree to participate in the trial by clicking the link will be asked to provide an email address and complete a brief 10-minute baseline questionnaire. Following completion of the baseline questionnaire, participants will immediately be given access to the web-based program (approximately 20 minutes), which will be followed immediately by the 10-minute posttest questionnaire survey. The 10-minute follow-up survey link will be sent to participants via email 6 months after completion of their allocated condition.

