#### Quality of Life

To measure the impact of the program on quality of life and for the economic evaluation, we will use the ReQoL-10 Questionnaire [46], which is a validated measure and highly suitable for measuring recovery and quality of life in the mental health context. The ReQoL-10 comprises 11 items, including 10 focused on mental health and 1 focused on physical health. The mental health items assess the frequency experienced over the last week of the thoughts, feelings, or activities mentioned, such as “I could do the things I wanted to do” and “I felt lonely,” assessed on a scale from 0=none of the time to 4=most or all of the time. Negatively worded items are reverse scored. The 11th item assesses the severity of physical health problems, including “problems with pain, mobility, difficulties caring for yourself or feeling physically unwell” experienced on a 5-point scale from 4=no problems to 0=very severe problems. The scale has been validated, with Cronbach α ranging from 0.87 to 0.92 [46,56], and has been used in economic evaluations of mental health interventions [57]. A UK-derived value set will be used to calculate utility values at each time point. The area under the curve method will be used to calculate QALYs from utility values.

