### Limitations and Risks

A potential but omnipresent risk in trials is that of recruitment; this risk involves recruiting insufficient participants to enable statistical power to detect intervention effects. We expect this risk to be moderate given that the Helipad trial is situated within a large clinical trials network (Mental Health Australis General Clinical Trials Network [64]), which will provide recruitment support through an extensive network and by directly providing contacts in workplaces. In addition, based on previous trials we have conducted, we have found that recruitment is typically highly successful in web-based trials, where we have previously engaged comparable number of participants [34-36], including in cluster-based universal web-based trials [37]. It may be challenging to retain the participants; however, given the instantaneous pre- and posttest design, attrition between these 2 time points may be less likely than in previous trials. Furthermore, as outlined in our data analysis plan, this risk is somewhat mitigated by conducting statistical analyses that account for all available data (ie, mixed effects models).

Moreover, there is an ethical risk that the intervention may provide information to participants that leads them to think they may be experiencing symptoms of common mental health problems (ie, psychological distress, anxiety, or depression). We intend to measure adverse events in our postintervention and 6-month follow-up surveys, which may capture these data. However, this forms a key part of the intervention, in that it is expected to prompt those who may not know they are experiencing symptoms of a common mental disorder to seek help. There is potential that such an experience may cause distress to a small proportion of people. We expect this risk to be low, as approximately 20% (180/900) of the participants are expected to have elevated symptoms, and this is unlikely to be surprising for many of these people. Given that the intervention is specifically designed to support this group, we will be providing specific resources, including how and where to seek treatment, to equip participants to access appropriate sources of help if this occurs.

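### Uncertainty in cost-effectiveness is stated only as bootstrap intervals on ICERs, which will be hard to read against the Aim 4 thresholds if the QALY difference may be zero

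*Protocol article*

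**What the plan says.** The Data Analysis section of the protocol article divides the between-arm difference in costs by the difference in QALYs to form an ICER, and adds: "Nonparametric bootstrapping will be used to determine CIs for ICERs". The Quality of Life section defines the denominator: "The area under the curve method will be used to calculate QALYs from utility values". Table 1 shows the utility instrument (ReQoL-10) at baseline and 6 months only.

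Under Exploratory Hypotheses (Aim 4), the program is expected to be cost-effective "relative to the willingness-to-pay thresholds identified by the Productivity Commission report on mental health".

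One further sentence in Data Analysis concerns other outcomes: "Additional ICERs using secondary outcomes will be calculated where the Helipad intervention is found to have an effect". That condition covers only the additional ICERs. The QALY ICER and its interval are to be produced whatever the QALY difference turns out to be.

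**The concern.** An interval for a ratio is easy to read when its denominator is clearly away from zero. Several features described in the article make that doubtful here. The program takes about 20 minutes, the comparator is an active, time-matched program, and only a minority of participants have much room to improve: "approximately 20% (180/900) of the participants are expected to have elevated symptoms". The introduction itself describes small symptom effects for universal workplace prevention programs. The trial is sized on help-seeking intentions at posttest, not on utility at 6 months.

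If replicates fall on both sides of zero QALYs, sorting them by ICER mixes opposite conclusions. The investigators would hold an interval that does not answer the Aim 4 question, and would have to choose another summary after seeing the data.

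**Working it through.** **No figure to reproduce.** The article gives no expected QALY difference, ICER, utility SD or numerical threshold. The sample size, intraclass correlation and cluster size below are taken as stated.

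**Why the ordering fails.** Take illustrative differences of 50 in cost and 0.00375 in QALYs (0.25 × 0.10 × an assumed utility SD of 0.15) and an illustrative threshold of 50,000 per QALY. Net benefit is 50,000 × QALY difference − cost difference.

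| Cost difference | QALY difference | ICER | Net benefit |
|---|---|---|---|
| −50 | +0.00375 | −13,333 | 187.5 + 50 = +237.5 |
| +50 | −0.00375 | −13,333 | −187.5 − 50 = −237.5 |
| +50 | +0.00375 | +13,333 | 187.5 − 50 = +137.5 |
| −50 | −0.00375 | +13,333 | −187.5 + 50 = −137.5 |

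Each ICER value arises from one favourable and one unfavourable result. Net benefit separates them.

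**How often zero QALYs cannot be excluded.**

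Inputs from Power and Recruitment: N = 900, intraclass correlation 0.02, cluster size 25 (the low end of 25 to 35, which favours the plan), 15% attrition to posttest. Assumed: attrition of 15, 30 or 50% at 6 months, since none is stated for that visit; a utility effect of d = 0.05 to 0.20 SD; and a baseline to 6-month correlation ρ of 0 (no gain from adjustment) or 0.6 (baseline-adjusted). The top value, d = 0.20, is the effect the article assumes for the primary outcome, not for utility.

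With two time points over half a year, QALY = 0.5 × (u0 + u6)/2 = 0.25 × (u0 + u6). Treating baseline as balanced, the QALY difference is 0.25 × the 6-month utility difference, so the utility SD cancels.

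- Design effect: DE = 1 + (m − 1) × 0.02, with m the analysed cluster size. At 15% attrition m = 21.25 and DE = 1.405.
- Standard error in SD units: SE = √(4 × DE / N × (1 − ρ²)), with N the number analysed. At 15% attrition and ρ = 0: √(4 × 1.405 / 765) = 0.0857.
- Chance that the 95% CI includes zero: 1 − [Φ(d/SE − 1.96) + Φ(−d/SE − 1.96)].

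| Attrition | ρ | SE | d = 0.05 | d = 0.10 | d = 0.15 | d = 0.20 |
|---|---|---|---|---|---|---|
| 15% | 0 | 0.0857 | 91% | 79% | 58% | 35% |
| 15% | 0.6 | 0.0686 | 89% | 69% | 41% | 17% |
| 30% | 0 | 0.0919 | 92% | 81% | 63% | 41% |
| 30% | 0.6 | 0.0735 | 90% | 73% | 47% | 22% |
| 50% | 0 | 0.1046 | 92% | 84% | 70% | 52% |
| 50% | 0.6 | 0.0837 | 91% | 78% | 57% | 33% |

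The rows with ρ = 0 still leave out chance baseline imbalance. A raw area-under-the-curve comparison has an SE larger by √(2(1 + r)), where r is the same baseline to 6-month correlation. At r = 0.6 and 15% attrition that is 1.789 × 0.0857 = 0.153, and the CI includes zero in about 90% of trials at d = 0.10 and 74% at d = 0.20.

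**Simulation.** A cluster bootstrap with 36 workplaces of 21 analysed participants (assumed utility SD 0.15, cost SD 800, true cost difference 50) gave QALY intervals that included zero in 90, 75 and 32% of trials at d = 0.05, 0.10 and 0.20. In one simulated trial at d = 0.10, 36% of replicates had a negative QALY difference. The percentile interval for the ICER ran from about −372,000 to +474,000, while net benefit at the illustrative 50,000 had an ordinary interval of −157 to 444. In that trial the share of replicates with an ICER below 50,000 (0.81) happened to be close to the share with positive net benefit (0.82). Over all simulated trials the two shares differed by more than 5 percentage points in 80, 59 and 19% at the three effect sizes.

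**The case against.** **The article is condensed, and the economic results will be published separately.** The plane, the acceptability curve and net benefit could all come from the planned replicates, and nothing excludes them. This stands: their absence is not in itself a fault, and a reader should not infer that the trial could never say whether the program is cost-effective. The point concerns the method that is stated.

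**No interval type is named.** This also stands, so a reader might go too far in calling the interval undefined or short of coverage. A percentile interval can always be printed, and in the simulation it covered the true ICER in 96, 98 and 97% of trials. The failure is one of interpretation. The Fieller alternative becomes unbounded when the denominator cannot be distinguished from zero.

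**The size depends on effect and adjustment.** A reader might infer that the problem arises in every scenario. It does not. With baseline adjustment, d = 0.20, a correlation of 0.6 and 85% retention, a trial whose estimate equals the true effect would have only about 0.2% of replicates below zero QALYs. Estimates vary between trials, however, and the QALY interval would still include zero in about 17% of them. At d = 0.10 or less the concern survives adjustment.

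**The additional ICERs.** Selecting on an observed effect tends to enlarge the denominator, so a reader might infer that the cost-effectiveness conclusion is biased. The article does not support that: Aim 4 names no secondary outcome, no threshold is given for one, and the QALY ICER is not selected in this way. Calculating those ratios whether or not an effect is found would be no remedy, because it would bring back the near-zero denominator.

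**Conclusion.** The point holds as a minor one. The stated interval does not match the stated hypothesis, and it becomes uninterpretable in the situation the article's own description makes plausible. Under assumed 6-month utility effects of d = 0.05 to 0.10, the QALY difference could not be distinguished from zero in about 69 to 92% of trials; at d = 0.20, in about 17 to 52%. These ranges rest on N = 900, an intraclass correlation of 0.02, attrition of 15 to 50% and baseline correlations of 0 or 0.6. The utility effect is an assumption throughout. Aim 4 is exploratory, so the primary and secondary effectiveness analyses are unaffected.

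**What to change.** Keep the point ICER. In Data Analysis, replace the sentence on intervals for ICERs with wording such as: *Uncertainty will be expressed as incremental net monetary benefit at each threshold referred to under Aim 4, with a nonparametric bootstrap 95% CI; the replicates will be shown on the cost-effectiveness plane and as an acceptability curve.*

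Leave the condition on the additional ICERs in place; at most, label those ratios as descriptive because they are selected on an observed effect.

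The cost is a change of wording. The bootstrap replicates are already planned, and no new data, participants or change in trial conduct are needed.
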